## Abstract

**BACKGROUND:**

Despite advances in TB care, approximately 2.4 million people with TB remain undiagnosed or unreported each year. A key contributor to these ‘missed millions’ is that major diagnostic gaps persist especially among underserved populations. Developing diagnostic algorithms that are accessible and integrated into health care systems where they are intended to be used is essential to meet WHO End TB targets.

**METHODS:**

Start4All a multi-country, cross-sectional diagnostic accuracy study (in Bangladesh, Brazil, Cameroon, Kenya, Malawi, Nigeria, and Viet Nam) aims to assess and model algorithms using combinations of WHO-endorsed, and experimental TB screening and diagnostic tests across the lowest levels of care and the community, compared to a sputum culture reference standard. Evaluated tools include C-reactive protein tests, computer-aided detection–interpreted chest X-rays, pooled Xpert® MTB/RIF Ultra (Xpert Ultra) testing, and a third generation lipoarabinomannan (LF-LAM) assay.

**DISCUSSION:**

Start4All will generate high-quality evidence to guide policy decisions on the adoption and the integration of non-sputum and laboratory independent tools to accelerate early TB detection and close the treatment gap.

**CONCLUSION:**

A feature of Start4All is its implementation within national TB programmes across seven high-burden countries to ensure that findings are directly translatable to policy and operational decision making. Harmonised protocols, standardised microbiological reference testing, and unified data management systems will enable cross-country comparison and strengthen the external validity of results.

Globally, TB remains the leading cause of death from a single infectious disease, despite being both preventable and curable when detected early. It is estimated that 10.7 million people fell ill with TB in 2024, with approximately 2.4 million of these people never being diagnosed, treated, or reported to national TB programmes (NTPs). This underserved group, often termed ‘the missed millions’, are considered a key driver of the 1.25 million deaths attributed to TB annually.^1,2^ TB affects all countries and age groups, but disproportionately impacts low- and middle-income countries (LMICs); all 30 of the highest TB-burden countries are classified as LMICs and together they account for 90% of the global TB burden. Efforts to end TB have been slow to meet elimination targets and were further impeded by the COVID-19 pandemic.^3^

Significant gaps remain in TB diagnosis, particularly at the lowest levels of the health system, where the majority of people first seek care.^4–6^ In many high-burden countries, reliance on symptom-based screening and poor access to diagnostic tests results in missed or delayed diagnoses. This is particularly true in people living with HIV (PLHIV) and children (people 14 years and younger), who often present with non-specific symptoms and paucibacillary disease,^7,8^ as well as other groups who face barriers in accessing health care, including economic and social.^9^ Diagnostic pathways frequently depend on sputum-based tests that are unavailable or inaccessible in peripheral facilities.^5^ Strengthening diagnostic strategies that combine simplified tools, decentralised technologies, and clear referral pathways at the primary care level is essential to address the TB treatment gap. Combining tests sequentially allows the inclusion of assays that individually might not have sufficient performance but as part of an algorithm capitalises on their strengths whilst mitigating individual limitations. This is especially useful for decentralised TB testing to allow tests that can capture a diverse range of TB symptoms and clinical presentations.

## Relevance of integrated, non-sputum and digital innovations at lower care levels

At lower levels of care, it is essential that technologies can be and are decentralised. Rapid molecular platforms, portable digital radiography systems combined with computer-aided detection (CAD) software for chest X-ray (CXR) interpretation, and biomarker-based assays that can be deployed outside of laboratories all exist, but require an evidence-based approach to maximise their impact and sustainability that is both context and population specific. Lessons should be learnt from the introduction of GeneXpert, which was positioned to revolutionise the way we test TB. However, programmatic evaluations have shown that it has frequently failed to reach peripheral facilities because of cost, infrastructure, and operational barriers, and has not been shown to improve TB treatment outcomes.^10,11^ Investment at the lowest levels of the health system and within the community is not only a matter of health care equity; earlier and more accurate diagnosis prevents disease progression, reduces the risk of severe complications, and can also be cost-saving.^12^ These cost savings are not only within health care systems, but are also important for people affected by TB, by reducing long-term treatment and associated costs.^13^

## Study description and objectives

The Start4All consortium is a Unitaid-funded research project comprising two distinct study phases (https://clinicaltrials.gov/study/NCT05845112). Phase 1 is a prospective diagnostic accuracy study designed to evaluate and model the algorithmic performance of TB screening and diagnostic tests across a diverse range of high-TB-burden countries, settings (e.g., primary health care facilities, district hospitals, and the community), and target populations (e.g., internally displaced people, nomadic groups, people living in informal settlements, those living rurally, urban low-income communities, and children [aged 1–14 years]). The screening and diagnostic tests to be evaluated as part of Phase 1 are pooled testing of sputum by Xpert Ultra, rapid and quantitative C-reactive protein (CRP), CAD-interpreted CXRs, and a third generation LF-LAM (see Supplementary Material 1) in people with presumptive pulmonary TB. Phase 2 aims to implement and evaluate the best performing modelled test algorithms across a subset of countries based on diagnostic performance, cost effectiveness, feasibility, acceptability and scalability. This protocol manuscript will only describe Start4All’s Phase 1 activities.

The objective of Phase 1 of Start4All is to evaluate, by country and setting, the performance of selected tests and model the performance of test algorithms for the diagnosis of TB at the lowest level of health care and within the community in countries with a high TB burden in the general population (Bangladesh, Brazil, Kenya, Nigeria), countries with a high burden of HIV-associated TB (Bangladesh, Cameroon, Kenya, Malawi, Nigeria), and countries with a high burden of drug-resistant TB (Bangladesh, Nigeria, and Viet Nam). A secondary objective will be to select the test algorithms per setting that have the best performance in comparison to the reference standard. Another secondary objective is to evaluate the performance of selected tests and pre-specified algorithms in aggregate analyses, by setting, but across multiple countries for each setting. Participants will be recruited through facility-based case finding (FBCF), including primary health care and district hospitals, and through community-based case finding (CBCF), also referred to as active case finding.

## METHODS

Start4All Phase 1 is a multi-country cross-sectional prospective diagnostic evaluation study of the performance of CRP (rapid diagnostic test and quantitative point of care platforms), CAD-interpreted CXRs, pooled testing of multiple sputum samples with a single Xpert Ultra cartridge, and third generation LF-LAM – individually and as pre-specified diagnostic algorithms. Where a test is not currently part of routine care, the results will not be shared with the clinical team and thus not interfere with routine clinical management.

### Study participants

Adults will be recruited from lowest level health care facilities (primary health care and district hospitals) across all countries and CBCF in Bangladesh, Cameroon, Nigeria, and Viet Nam. Adults are categorised as 15 years of age and above in Bangladesh, Cameroon, Kenya, Nigeria, and Viet Nam and 18 years of age and above in Brazil and Malawi. Children will be recruited from health care facilities (primary health care and district hospitals) from Cameroon and Viet Nam. Children are categorised as 1–14 years inclusive.

### Eligibility and inclusion criteria

Start4All will consecutively recruit adults (all countries) and children (Cameroon and Viet Nam) with presumptive pulmonary TB as characterised by the WHO four symptom screen^14^ (W4SS; cough, fever, night sweats, weight loss) from health care facilities (see Supplementary Material 2 for full symptom criteria). Individuals screening positive and eligible for inclusion will be invited to a private area of the health care facility and provided further details of the Start4All study and, if willing to participate, written informed consent will be sought (Supplementary Material 3). For children and young adolescents, written informed consent will be obtained from a parent or guardian at the time of enrolment and assent signed for those aged 15 years to age of majority in the respective country.

### Community-based case finding

In Bangladesh, Cameroon, Nigeria, and Viet Nam, adults will be consecutively recruited through CBCF initiatives. Based on local context, CBCF will be conducted in informal urban settlements in Bangladesh, rural communities in Cameroon, and amongst nomadic and internally displaced populations in Nigeria and urban low-income communities in Viet Nam. The CBCF will be organised through lung health camps. There will be community sensitisation drives before the health camps to invite people to participate in the camp. All individuals who are interested in being evaluated for lung disease attending the camp will be screened upon contact by both W4SS, under the same parameters as in health care facilities, and by CXR. A posterior-anterior (PA) X-ray will be taken from all individuals and interpreted by CAD software (qXR, Qure.ai, Mumbai, India). Any individuals that have a CAD software abnormality score of ≥0.3, living with HIV and/or a household contact will be eligible for study entry irrespective of symptoms. The threshold of ≥0.3 has been selected based on previous work conducted within our study countries for CBCF activities.^15^

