### Participant flow

For individuals recruited via community-based screening, a CXR will be taken prior to study enrolment, supported by the national NTP as routine practice in CBCF activities. For those recruited via facility-based screening, CXR will occur after study enrolment. Individuals who meet the eligibility criteria will then be invited to a private room within the health care facility, provided with a patient information leaflet, and given an opportunity to ask any questions about participation. They will be ensured their decision to agree or decline the invitation will not negatively impact their routine care. Following written informed consent, individuals will be interviewed by the Start4All study team and a comprehensive case report form (CRF) will be taken (Supplementary Material 3). This will include key demographics, TB history – both personal and household – and data on associated TB risk factors. Participants will then be asked to provide two spot sputum samples 30 minutes apart, whole blood, a CXR (for those enrolled via FBCF), and urine. The Figure outlines the specimen collection procedure and testing conducted as part of the study. For children, where sufficient sputum samples cannot be obtained, per national guidelines, one or more of the following specimens will be taken to allow reference standard testing: induced sputum, gastric aspirate, nasopharyngeal aspirate, and stool. In Cameroon, venous whole blood will be used as this is routine clinical practice, but for all other countries capillary whole blood will be used from a single finger prick sample. For all adults, only one PA CXR will be taken. Thus, for individuals recruited through CBCF, the CXR taken during pre-consent eligibility screening will be used for CAD software processing, while those recruited through FBCF, will have their CXR taken and processed with the CAD software following study enrolment. For children aged <10, an additional lateral CXR image will be taken.

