## TEST METHODS

### Microbiological reference standard (MRS)

The microbiological reference standard in this evaluation will be mycobacteria growth indicator tube culture, for all countries except Brazil, where, as is routine practice, solid culture using Löwenstein–Jensen media will be used. The results of the MRS will not be disclosed to the laboratory personnel performing the experimental test evaluations.

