### Experimental test selection

As part of Start4All Phase 1, two classes of WHO-recommended TB screening tests will be evaluated: CRP and CXRs interpreted by CAD software. However, both are restricted to use in specific populations, with CRP limited to PLHIV and CXR with CAD in adolescents and adults aged ≥15 years in place of human interpreters. Concurrently, using the molecular WHO-recommended low complexity nucleic acid amplification test (LC-NAAT) Xpert Ultra, the strategy of pooling sputum samples from multiple individuals and testing with one cartridge will also be investigated, hereby known as pooled testing. In Start4All, this will preferentially be a pool ratio of 4:1, but if an odd number of specimens are collected (e.g., not evenly divisible by four) or sufficient specimens are not available, ratios of 3:1 and 2:1 will be performed. Finally, a new (third) generation LF-LAM assay will be evaluated for diagnostic accuracy across the general population and not just in PLHIV, a population which is not currently recommended for LAM testing by WHO. Supplementary Data S4 describes all experimental tests used as part of this study. Experimental test results will not be shared with the clinical team and so will not influence clinical management. The only exceptions are in Cameroon where pooling of sputum is routinely implemented to optimise cartridge use and in Bangladesh where CAD interpretation of CXRs is being routinely used by the NTP.

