## DATA COLLECTION AND ANALYSIS

As a prospective diagnostic accuracy study, reporting will follow the diagnostic accuracy studies (STARD) standard.^17^ The metrics to be included will be sensitivity, specificity, and positive and negative predictive values.

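### In community case finding the CAD score is both an entry route and an index test, so CAD sensitivity is too high and specificity too low at the 0.3 cut-off relative to camp attendees

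*Protocol article*

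**What the plan says.** Under Experimental test selection, "two classes of WHO-recommended TB screening tests will be evaluated: CRP and CXRs interpreted by CAD software". Under Data collection and analysis, "The metrics to be included will be sensitivity, specificity, and positive and negative predictive values". Study description and objectives asks for performance by country and setting.

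Under Community-based case finding, all attendees at a lung health camp "will be screened upon contact by both W4SS, under the same parameters as in health care facilities, and by CXR". Then "Any individuals that have a CAD software abnormality score of ≥0.3, living with HIV and/or a household contact will be eligible for study entry", whatever their symptoms. A positive symptom screen is presumably an entry route too, since it is applied as in facilities, although the section does not say so outright.

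Under Participant flow, adults have only one film. For community recruits, "the CXR taken during pre-consent eligibility screening will be used for CAD software processing". Specimens come after consent: "Participants will then be asked to provide two spot sputum samples 30 minutes apart, whole blood, a CXR (for those enrolled via FBCF), and urine". Those specimens are what the reference standard needs: "The microbiological reference standard in this evaluation will be mycobacteria growth indicator tube culture, for all countries except Brazil", where solid culture is used.

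The facility arm differs: "For those recruited via facility-based screening, CXR will occur after study enrolment". CAD cannot influence entry there.

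**The concern.** A community attendee with a CAD score below 0.3, no symptoms, no known HIV and no household contact is not enrolled, gives no sputum and is never cultured. The people lost this way are CAD false negatives if they have TB and CAD true negatives if they do not. This is partial verification driven by the index test.

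Among participants who entered on the CAD score alone, sensitivity at 0.3 is 100% and specificity 0% by construction, whatever the software does. Mixing them with participants who entered by other routes gives a figure that describes neither camp attendees nor the symptomatic or risk-group population.

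Reweighting cannot repair this, because the excluded group has zero probability of verification. At stake is the community estimate for a main index test and, through it, the choice of algorithms for Phase 2, which rests partly on diagnostic performance. An inflated sensitivity could favour CAD-first community algorithms.

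**Working it through.** **Scale for comparison.** Table 1 uses n = p(1 − p)(1.96/E)² with p = 0.9. For E = 5, 6, 7, 8, 10 and 15% this gives 138.3, 96.0, 70.6, 54.0, 34.6 and 15.4, which round up to the stated 139, 97, 71, 55, 35 and 16. The plan's precision targets for sensitivity are thus 5 to 15 points.

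**General form.** Let f1 and f0 be the shares of CAD <0.3 attendees, with and without TB, who enter by another route. At the 0.3 cut-off:
- observed sensitivity = Se / [Se + (1 − Se)·f1]
- observed specificity = Sp·f0 / [Sp·f0 + (1 − Sp)]

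Both equal the true value only if f1 = f0 = 1. Prevalence cancels. The documents give none of Se, Sp, f1 or f0, so what follows rests on assumptions.
- True Se 0.80 with f1 = 0.2, 0.5, 0.7 is observed as 0.952, 0.889, 0.851: a bias of about 5 to 15 points.
- True Sp 0.80 with f0 = 0.1, 0.3, 0.5 is observed as 0.286, 0.545, 0.667.

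**Illustration by entry route.** Assume that half of TB is symptom-negative; that CAD sensitivity at 0.3 is 90% in symptomatic and 70% in asymptomatic TB; that specificity is 80% in symptomatic and 93% in asymptomatic people without TB; that 20% of people without TB are symptom-positive; that symptom-positive people enter at any score; and that a share g of asymptomatic attendees enters through HIV or contact.
- True sensitivity: 0.5×0.9 + 0.5×0.7 = 0.80. Observed: 0.80/(0.5 + 0.35 + 0.15g). At g = 0 this is 0.80/0.85 = 94.1%; at g = 0.1 it is 0.80/0.865 = 92.5%.
- True specificity: 0.2×0.80 + 0.8×0.93 = 0.904. Observed: (0.16 + 0.744g)/(0.256 + 0.744g). At g = 0 this is 62.5%; at g = 0.1 it is 0.2344/0.3304 = 70.9%.

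**Range for sensitivity.** Let a be the asymptomatic share of TB and s the CAD sensitivity in asymptomatic TB. Observed = true / [1 − a(1 − s)(1 − g)].

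| a | s | g | True | Observed | Bias (points) |
|---|---|---|---|---|---|
| 0.7 | 0.6 | 0 | 0.69 | 0.69/0.72 = 0.958 | 26.8 |
| 0.5 | 0.7 | 0.5 | 0.80 | 0.80/0.925 = 0.865 | 6.5 |
| 0.3 | 0.8 | 0.1 | 0.87 | 0.87/0.946 = 0.920 | 5.0 |
| 0.3 | 0.8 | 0.5 | 0.87 | 0.87/0.97 = 0.897 | 2.7 |

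**Other cut-offs.** Take true Se/Sp of 0.90/0.80 at 0.3, f1 = 0.5 and f0 = 0.3, with the same entry shares at all scores below 0.3. The enrolled shares are 0.90 + 0.10×0.5 = 0.95 of TB and 0.20 + 0.80×0.3 = 0.44 of non-TB.
- Higher cut-off, true 0.80/0.90: observed 0.80/0.95 = 0.842 and 1 − 0.10/0.44 = 0.773.
- Lower cut-off, true 0.95/0.70: observed 0.925/0.95 = 0.974 and 0.21/0.44 = 0.477.

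**CAD then Xpert** (Xpert assumed 0.90/0.99, conditionally independent, same entry shares). True values are 0.810 and 0.998; observed 0.81/0.95 = 0.853 and 1 − 0.002/0.44 = 0.995. Sensitivity moves by about 4 points and specificity hardly at all.

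**Predictive values.** The score admits everyone at 0.3 or above, so this rule does not distort PPV at those cut-offs. NPV rests only on the enrolled, higher-risk people below 0.3.

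**Check of the fix.** In the illustration at g = 0, restricting to people who qualify without CAD gives 0.45/0.50 = 90% sensitivity and 0.16/0.20 = 80% specificity. These are the true values for that group, and not the camp-wide 80% and 90.4%.

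**The case against.** The strongest reply is that the plan evaluates tests in people with presumptive pulmonary TB and never claims camp-wide accuracy. Everyone meeting the entry rule is to have culture, so the estimates are internally valid for that group. This is true as far as it goes. But in the community arm the group is partly defined by a CAD score of 0.3 or more, so the accuracy of CAD in it is circular and does not describe CAD as a camp screen.

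A reader might infer more than the documents support:
- *That CAD alone decides who is enrolled.* It does not. HIV, household contact and presumably symptoms admit people at any score, so the bias is partial. The 100%/0% result applies only to CAD-only entrants and only at 0.3, which is set as an entry threshold and not as the positivity cut-off for the index test.
- *That a particular size is established.* The inputs are assumed. People with HIV and contacts may be over-represented among asymptomatic TB cases, which shrinks the bias, as the rows with g = 0.5 show. In the other direction, HIV testing is not routine at the Viet Nam sites or among people with TB in Bangladesh, which weakens that route there. Excluding miliary TB seen on the film probably pulls sensitivity slightly down.
- *That every algorithm containing CAD is distorted alike.* CAD-then-Xpert specificity barely changes. For algorithms positive on CAD or another test, the direction is likely but not certain: it depends on whether the algorithm detects fewer of the excluded TB cases than of TB cases overall.

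It can also be said that stratified analysis belongs in the analysis plan or the supplements, which are not shown, and that aggregate analyses are already planned by setting. Both are fair on analysis detail. But the entry rule and the reuse of the film are fixed in this article, and no later analysis can recover an unverified group without untestable assumptions.

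**Conclusion.** The concern holds in a limited form. In the community arm, in four of seven countries, one pre-consent film serves as an entry route and as the index test, and attendees below 0.3 with no other route have no reference standard. Relative to camp attendees, CAD sensitivity at 0.3 is too high and specificity too low unless every such attendee enters some other way.

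The direction follows from the text; the size does not. Under the assumed inputs sensitivity is overstated by roughly 3 to 27 points, which spans the plan's own 5 to 15 point precision targets, and a larger sample would not reduce it. These figures take the favourable reading that symptom-positive people enter at any score; otherwise the bias is larger. Facility estimates are unaffected.

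**What to change.** State that in community case finding the primary accuracy analysis of CAD, and of algorithms containing CAD, uses only participants who qualify without the CAD score: symptom-positive, living with HIV, or a household contact. Label the result as accuracy in that population. Classify by status known at screening. HIV tests offered after enrolment, as in Cameroon and Nigeria, could otherwise move CAD-only entrants into this group.

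Report CAD-only entrants separately, as yield and PPV and as accuracy of the downstream tests given a score of 0.3 or more. Claim no CAD sensitivity or specificity for them, and keep them out of pooled CAD estimates. Record the entry route for each community participant; the article does not say that this is done.

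The cost is fewer participants and a wider interval for the community CAD estimate, which still does not give camp-wide accuracy. If that is wanted, a random sample of the otherwise excluded attendees would need culture, weighted by the inverse sampling fraction. In expectation this returns the true values (0.80/0.80, against a naive 0.889/0.545 at f1 = 0.5 and f0 = 0.3), but it means additional enrolment and culture.
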